#### Determination of sample size

In compliance with current recommendations for non-superiority trials [34], a minimum sample size has been estimated for two scenarios:

The superiority scenario assumes that XR-NTX participants will have opioid-negative samples on a mean of 7 out of the total 12 (7/12 or 0.58) samples, while participants receiving buprenorphine-naloxone will display a mean of 4 opioid-negative samples (4/12 or 0.33). With a 95 % significance level (*p* < 0.05) and a standard deviation of 3 in both medication groups, and power (beta) set to 90 %, a sample size of 17 patients/medication arm or *n* = 34 total is estimated to be sufficient for analysis. The estimated frequency of opioid use in each group is based on data from Norwegian patients receiving sustained release naltrexone [22] or on the frequency of illicit opioid use during buprenorphine maintenance in the Norwegian national ART program.

In the non-superiority scenario, using a beta of 90 %, we assume that both groups will retain 70 % of their participants at the end of Week 12 and set 20 % as the non-superiority margin; this yields a minimum sample size of *n* = 58 in each group/*n* = 116 total.

Based on the sample size calculations and the risk of dropout of a significant proportion of participants, we have set the recruitment target for *n* = 180 total, or *n* = 90 for each medication group. This will be facilitated by characteristics of design (few exclusion criteria, open-label allocation, outpatient data collection often coinciding with medication and counseling), prioritization of amount–and types of data collected. Information about the study will be distributed at clinical sites as well as outreach -, housing- and criminal justice facilities and the internet; these efforts are anticipated to attract the initial *n* = 30 patients whose presence in the larger community of opioid users will be sufficiently inform more potential participants to contact study staff for information.

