### Statistical analyses

Statistical analyses on the randomized part of the study will be conducted by a non-study statistician on a final RCT data set in which the two study medications is masked as ‘Rx A’ and ‘Rx B’; any obvious characteristics of the two comparison medications will also be censored before data are made available for analysis. For between- group comparisons and to control for the effect of baseline characteristics, we will use a General Linear Mixed Models (GLMM) approach containing factors for treatment group, sex, and sex-by- treatment interaction, and with age, duration of opioid dependence, and duration of last pre-study inpatient detoxification as covariates. For outcomes violating the normality assumption, a General Alinear Mixed Models (GAMM) approach will be used. Regular statistics (e.g. ANOVA, linear regression) may be utilized if the arguments for using GLMM or GAMM over legacy analysis types are considered to provide limited benefit. Retention will be assessed with Kaplan-Meier curves and a log-rank test. Adverse events will be compared using Fisher’s exact test. The primary endpoints are tested with a two-sided α = 0.05. Where relevant, *p* values will be adjusted for multiplicity using the Bonferroni-Holm method to preserve family-wise type 1 error at 0.05. Once the statistician concludes data analysis of the RCT phase, study management will be able to access the final dataset.

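### At the plan's two-sided 5% level, the superiority sample size of 17 per arm gives about 81% power, not 90%; the stated inputs need 22 to 23 per arm

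*Protocol article*

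**What the plan says.** The Determination of sample size section gives every input of the superiority scenario:

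- Means: "XR-NTX participants will have opioid-negative samples on a mean of 7 out of the total 12", while "participants receiving buprenorphine-naloxone will display a mean of 4 opioid-negative samples".
- Spread and power: a standard deviation of 3 "in both medication groups, and power (beta) set to" 90%.
- Level: a p-value threshold of 0.05, with no sidedness given.
- Result: 17 patients per arm, 34 in total.

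The sidedness is in the Statistical analyses section: "The primary endpoints are tested with a two-sided α = 0.05". Allocation is 1:1 (Randomization section). Abstinence from illicit opioids in urine drug tests is named among the primary outcomes in the abstract.

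The recruitment target is 180, or 90 per arm. The article bases it on this calculation, on the non-superiority calculation for retention (58 per group), and on an allowance for dropout.

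**The concern.** The article prints the inputs, the level, the power and the answer, and the answer does not follow from the rest. A standardised difference of 1.0 tested at two-sided 5% with 90% power needs more than 17 patients per arm.

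This is one of only two calculations offered in support of the sample size, and it concerns a primary outcome. A reader who takes it at face value would believe that 34 patients leave a 10% chance of missing the assumed effect. At the plan's two-sided level that chance is 17% to 19%.

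The label adds to the confusion. Beta is the type II error and power is 1 − beta. Calling 90% beta, as both scenarios do, is wrong and makes it harder to see which setting produced the figure.

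**Working it through.** **Inputs.** Difference 7 − 4 = 3; SD 3 in both arms; standardised difference d = 3/3 = 1.0 (Determination of sample size). Alpha 0.05, two-sided (Statistical analyses). Power 90% (Determination of sample size). Allocation 1:1 (Randomization).

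**Formula (normal approximation).** n per arm = 2 × (z for alpha + z for power)² / d².

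**Step 1: try to reproduce 17 per arm.** Unrounded requirements per arm:

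| Setting | Normal approximation | t-test |
|---|---|---|
| Two-sided 5%, 90% power (as stated) | 21.01 → 22 | 22.02 → 23 |
| Two-sided 5%, 80% power | 15.70 → 16 | 16.71 → 17 |
| One-sided 5%, 90% power | 17.13 → 18 | 17.85 → 18 |
| One-sided 5%, 80% power | 12.37 → 13 | 13.10 → 14 |

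The stated setting in full: 2 × (1.960 + 1.2816)² / 1² = 21.01, rounded up to 22.

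Only two-sided 5% with 80% power, by t-test, gives exactly 17 after rounding up. One-sided 5% with 90% power comes close: 17.13 becomes 17 if rounded to the nearest whole number.

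**Step 2: power at 17 per arm, two-sided 5%.** Normal approximation: Φ(d × √(n/2) − 1.960) = Φ(√8.5 − 1.960) = Φ(2.916 − 1.960) = Φ(0.956) = 83.0%. The noncentral t gives 80.7%.

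**Step 3: power at other sizes, two-sided 5%.**

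| n per arm | Normal approximation | t-test |
|---|---|---|
| 17 | 83.0% | 80.7% |
| 22 | 91.3% | 89.97% |
| 23 | 92.4% | 91.2% |
| 58 | above 99.9% | above 99.9% |
| 90 | above 99.9% | above 99.9% |

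**Step 4: could rounding of the SD explain it?** For 17 per arm to give 90% power at two-sided 5% by the normal approximation, the SD would have to be 3 / (√(2/17) × 3.2415) = 2.70. The article states 3 for both groups.

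**The case against.** The best defence is that the sample size paragraph does not state sidedness. With a one-sided 5% test, 17 per arm gives 89.8% (normal) or 88.6% (t-test), which is close to the stated 90%. The figure may therefore come from a one-sided setting, not from a slip in the arithmetic. As an account of its origin this is plausible, and the document does not settle it. It does not make the statements consistent, because the Statistical analyses section prescribes two-sided testing of the primary endpoints. Rounded up properly, the one-sided calculation also gives 18.

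A second point is that the main planned analysis is a mixed model with sex, a sex-by-treatment interaction and covariates, so an unadjusted t-test is only a stand-in. That is fair. The 81% measures the figure against the stated two-sided level, not against the exact planned model. However, the paragraph itself works from two means and a common SD, so the two-sample comparison is the right check of its arithmetic.

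The third point is that nothing in the conduct of the trial depends on 17 versus 23. This stands in full. The article calls these minimum sizes, the other scenario asks for 58 per group, the target is 90 per arm, the study is described as exploratory, and recruitment is reported as having run to July 2015.

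**Conclusion.** The discrepancy is real. Under the article's own inputs and its two-sided 5% level, 17 per arm gives 80.7% power (t-test) or 83.0% (normal approximation). The stated 90% needs 22 or 23 per arm, so the printed figure is 5 to 6 patients per arm short. At least one of the printed size, power or sidedness must be wrong; the document does not show which.

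The result rests on a two-sample comparison of means with d = 1.0 and equal arms, with no dropout allowance and no adjustment of alpha for several primary outcomes. A smaller alpha under the Bonferroni-Holm procedure would lower power at 17 per arm further. The article does not define the family of tests, so no figure for that is relied on here.

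The consequence is confined to the sample size justification. At 90 per arm, power for this effect exceeds 99.9%, so the recruitment target is not at risk on this endpoint. The retention calculation is a separate matter and is not needed for this conclusion.

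**What to change.** Correct the superiority sentence in one of two ways:

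- Keep 90% power and state 23 patients per arm, 46 in total (two-sided alpha 0.05, t-test); or
- Keep 17 per arm, 34 in total, and state 80% power (two-sided alpha 0.05, t-test).

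In either case, state the sidedness in the sample size paragraph so that it agrees with the Statistical analyses section, and write the power as 90% (beta 10%), or 80% (beta 20%) if 17 is kept. Correct the same label in the non-superiority paragraph. Add that at 180 patients the power for this endpoint exceeds 99% under the stated inputs, so the retention scenario is the one that determines the size.

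The cost is a sentence or two of text. Recruitment, conduct and analysis do not change.

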**Methods/Design:**

In this five-hospital RCT with long-term follow-up, we aim to recruit *n* = 180 patients in treatment for opioid dependence and allocate them in an open, randomized manner (1:1) to receive either 4-week XR-NTX or daily buprenorphine-naloxone (BP-NLX) for the duration of 12 weeks. Allocation is open-label due to the risk of overdose during attempts to self-unmask allocation using heroin. Urine drug tests are scheduled every week with follow-up visits & assessment every 4 weeks. Primary outcomes are abstinence from illicit opioids in urine drug tests and self-report, as well as retention in treatment. Secondary outcomes include other substance use, injecting behavior, drug craving, mental health, quality of life, treatment satisfaction, abstinence motivation, opioid agonist effect rating, insomnia, and pain. Observation is continued for another 36 weeks in order to assess longer-term safety, adherence and effectiveness. The study is an investigator-initiated trial, funded by public grants and approved by an Independent Ethical Committee (the Regional Ethical Committee for Research South-East B # 2011/1320) and the Norwegian Medicines Agency.

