### Randomization

Allocation is conducted by non-study personnel on a per-patient basis using a permuted block algorithm accessible via a computer program with full-entry tracking. Participants are randomly allocated with a 1:1 ratio to either XR-NTX or BP-NLX independent of site, setting (clinic or criminal justice) or gender. When a study staff member contacts allocation staff for inclusion and randomization, inclusion criteria are verified before the patient is formally included into the database and allocated to one of the two medication groups. Group allocation is communicated openly to study staff via telephone, who are then free to communicate the results of the allocation procedure to patient and clinical staff in an open-label manner.

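### The 58 per group for the Week 12 retention margin does not follow from its stated inputs: it gives about 65% power, not 90%, and the target of 180 gives 83% at two-sided 0.05

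*Protocol article*

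**What the plan says.** The section Determination of sample size opens the second scenario with "In the non-superiority scenario, using a beta of 90" per cent, which can only mean 90% power. It continues: "we assume that both groups will retain 70 % of their participants at the end of Week 12". It takes 20% "as the non-superiority margin; this yields a minimum sample size of" 58 in each group, 116 in total. The recruitment target is then set at 180 (90 per group), on the strength of the sample size calculations and expected dropout.

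That paragraph gives no significance level for this scenario. Statistical analyses does, for all primary endpoints: "The primary endpoints are tested with a two-sided α = 0.05". Retention is one of these, since the Abstract (Methods/Design) states: "Primary outcomes are abstinence from illicit opioids in urine drug tests and self-report, as well as retention in treatment". Allocation is equal: "Participants are randomly allocated with a 1:1 ratio to either XR-NTX or BP-NLX" (Randomization).

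**The concern.** Every input needed to check the 58 is printed, and 58 looks far too small for a 20-point margin around a 70% rate. Equal true rates plus a margin is a non-inferiority calculation, so the article's term non-superiority is read that way here.

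The main research question asks whether XR-NTX is more effective than, or equally effective to, BP-NLX. The second conclusion rests on this calculation alone. The superiority scenario needs only 34 patients in total, so 116 is the figure that governs and that 180 builds on. A reader who sees a 116-patient minimum at 90% power and a target of 180 will infer power well above 90%. An inconclusive retention result would then be read as evidence of a real difference more readily than the design allows.

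**Working it through.** **Inputs**

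| Input | Value | Source |
|---|---|---|
| Week 12 retention, both groups | 0.70 | Determination of sample size |
| Margin | 0.20 absolute | Determination of sample size |
| Power | 90% | Determination of sample size |
| Significance level | two-sided 0.05, so one-sided 0.025 for a one-directional margin test | Statistical analyses (carried over) |
| Allocation | 1:1 | Randomization |
| Stated minimum | 58 per group | Determination of sample size |
| Target | 90 per group | Determination of sample size |

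**Step 1: try to reproduce 58.** The two-group variance term is 0.7 × 0.3 + 0.7 × 0.3 = 0.42. Then

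n per group = 0.42 × (z_alpha + z_beta)² / 0.20² = 10.5 × (z_alpha + z_beta)².

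| One-sided alpha | Power | Calculation | n per group |
|---|---|---|---|
| 0.025 | 90% | 10.5 × (1.960 + 1.282)² = 110.3 | 111 |
| 0.05 | 90% | 10.5 × (1.645 + 1.282)² = 89.9 | 90 |
| 0.10 | 90% | 10.5 × (1.282 + 1.282)² = 69.0 | 69 |
| 0.025 | 80% | 10.5 × (1.960 + 0.842)² = 82.4 | 83 |
| 0.05 | 80% | 10.5 × (1.645 + 0.842)² = 64.9 | 65 |

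None gives 58. The Farrington-Manning variance gives 110 per group at one-sided 0.025 and 90% power. A two-sided equivalence test (two one-sided tests) at 90% power needs 137 or 114 per group, at 0.025 or 0.05 for each one-sided test.

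**Step 2: what would give about 58?** Only a changed input or an invalid formula:

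- A 25-point margin at one-sided 5%: 0.42 × (1.645 + 1.282)² / 0.25² = 57.5, so 58.
- About 75% power at one-sided 5%: 57.
- About 85% power at one-sided 10%: 57.
- A continuity-corrected superiority test of 0.7 against 0.9 at one-sided 5% and 80% power: 58.
- Leaving out one group's variance at one-sided 2.5%: 0.21 × (1.960 + 1.282)² / 0.04 = 55.2, so 56. This is not a valid two-group calculation.

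The article does not show which of these, if any, was used.

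**Step 3: power delivered.** Power = Phi(0.20 / sqrt(0.42/n) − z_alpha).

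| n per group | 0.20 / sqrt(0.42/n) | One-sided 0.025 | One-sided 0.05 |
|---|---|---|---|
| 58 | 2.350 | Phi(0.390) = 65.2% | Phi(0.705) = 76.0% |
| 90 | 2.928 | Phi(0.968) = 83.3% | Phi(1.283) = 90.0% |

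Exact binomial enumeration at one-sided 0.025 gives 64.8% and 83.3%. Farrington-Manning gives 65.7% and 83.7%.

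**Step 4: the margin that 58 per group can test with 90% power.** (1.960 + 1.282) × sqrt(0.42/58) = 0.276, or 27.6 points. At one-sided 5% it is (1.645 + 1.282) × sqrt(0.42/58) = 0.249, or 24.9 points.

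**Step 5: a conditional figure.** Statistical analyses applies Bonferroni-Holm where relevant. If it covered three primary outcomes and retention were tested at the first step, one-sided alpha would be 0.05/3/2 = 0.0083, and power at 90 per group would be Phi(2.928 − 2.394) = 70%. The article does not say that Holm covers the margin test, so this is an assumption.

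**The case against.** The strongest reply accepts that 58 is wrong but limits what follows from it.

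- **Significance level.** The sample size paragraph states none, so two-sided 0.05 is carried over from Statistical analyses. At one-sided 5% the target of 90 per group is exactly what 90% power needs. This stands as a condition on the shortfall at 180. It does not rescue 58, which gives 76% even then.
- **Dropout.** The article sets one target for the whole trial. Dropout does cost data for the urine and self-report outcomes, and for the completer, modified intention-to-treat and per-protocol sets in Analysis sets. This stands for those analyses. For Week 12 retention with all randomised patients counted, a dropout is simply a patient not retained and is already in the 70% assumption. The extra patients do raise power there, but they do not offset any loss.
- **Power at 180.** The article claims none, and Study design calls the approach exploratory. Both are true. The 90% attached to 58 per group is still printed and wrong, and the inference drawn for 180 is a natural one.
- **Timing.** Participants & setting reports recruitment from November 2012 to July 2015, so silently replacing the planning figure would misrepresent history. That is a fair point about how the correction is made.

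**Conclusion.** The concern holds. With 70% retention in both groups, a 20-point margin and 90% power, 58 per group is wrong at every conventional significance level. At the only level the article states for primary endpoints, the requirement is 111 per group, so the printed figure is 111 − 58 = 53 per group too small and delivers about 65% power.

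The target of 180 gives 83% at that level and 90% at one-sided 5%. Both figures assume equal true retention of 70% and that all 90 per group are analysed. Any exclusion of randomised patients lowers them. The failure of 58 does not depend on the choice between the two levels; the shortfall at 180 does.

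**What to change.** Correct the paragraph in Determination of sample size, and disclose it as a correction because recruitment is over:

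1. State the significance level of the margin test. Under two-sided 0.05 (one-sided 2.5%), replace 58 per group and 116 in total with 111 per group and 222 in total for 90% power, noting that 58/116 was the planning figure and was in error.
2. State what the trial delivers, for example: with n = 180 and all randomised patients analysed, power to exclude a 20-point deficit in Week 12 retention is 83% at one-sided 2.5% (90% only at one-sided 5%).
3. Make clear that the dropout allowance serves the urine and self-report outcomes and the reduced analysis sets, and is not headroom for Week 12 retention.
4. If the 58 came from an input that is not printed, such as another margin or level, say so. The margin should not be changed after the fact to fit the number.

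The cost is the wording of one paragraph and a less favourable power statement. No further enrolment and no change to trial conduct is needed.

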#### Analysis sets

In addition to analyses of data from all patients who complete the 12-Week study, Intention-to-treat (ITT) analyses of efficacy endpoints will be conducted with all patient data. Separate analyses sets may be conducted on different analysis sets depending on publication requirements: e.g. a modified intention to treat (MITT) set of randomized patients who receive at least one dose of their assigned medication and complete at least one study follow-up; or a per-protocol dataset of patients who exhibit compliance with medication–and attend all four outpatient follow-ups. Imputation will be conducted using the previous valid assessment (last observation carried forward) at the last attended study follow-up or (if no follow-up took place) from the inclusion dataset; imputation using data modeling may be considered pending satisfactory similarity to collected data. The inclusion dataset may be corrected for days spent in a controlled environment (e.g. on-site detoxification unit) in order to convey the most accurate picture of pre-study functioning. For analyses beyond the 84-day randomized period, imputation (e.g. ITT, MITT) will only be conducted if considered relevant to the research question.

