#### Pre-randomization tapering of opioid agonists

As naltrexone may induce withdrawal symptoms by displacing any opioid agonists at opioid receptor sites, they are assisted in tapering and detoxification in order to facilitate the transition with as low a risk as possible. Detoxification and induction on to study medication is conducted in a controlled environment, usually an on-site inpatient detoxification unit. Only patients unwilling or assessed as unable to undergo inpatient detoxification, an outpatient detoxification with daily staff contact can be arranged with daily or bi-daily urine drug screening.

Buprenorphine is the recommended medication for alleviating opioid withdrawal symptoms during detoxification in Norway, and is administered to all participants at the discretion of the on-site treating physician. A higher dose is typically administered to ART patients habituated to a daily buprenorphine dose (16 mg/buprenorphine is the standard target dose in ART) tapered for a standard 2 mg/day, while a lower dose (2–4 mg buprenorphine/day) is typically administered to illicit heroin users. Any regular methadone users are required to taper down and discontinue methadone for a minimum of 72 h before randomization. Once participants are stable in the 0–4 mg buprenorphine/day range, they are considered ready for random allocation (1:1) to either standard treatment with buprenorphine-naloxone (target dosage 16 mg/day, range 4–24 mg) or extended-release naltrexone (XR-NTX) 380 mg every 28 days, for the upcoming 12 weeks/84 days.

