#### Regulatory approvals, data–and safety monitoring

The Common Terminology Criteria for Adverse Events (CTCAE) version 4 is used to classify adverse events at follow-up. Any event requiring medical intervention is registered (CTCAE level 2 or above). Medication-related Severe Adverse Events (SAEs) and Sudden Unexpected Severe Adverse Reactions (SUSARS) are reported to the Norwegian Medicines Agency (European Medicines Agency) and to the study drug manufacturers (Alkermes, Inc. and Reckitt-Benckiser, Inc.) within two working days. No interim analyses are planned, but the Sponsor (the University of Oslo, Norway) as well as regulatory authorities may stop recruitment and further medication with study medication in the case of an emergency, e.g. an unusual accumulation of SAEs or SUSARs attributable to study medication.

As all participants are enrolled in a local ART clinic, ART services are assigned the legal responsibility for monitoring of everyday safety of the patient with the option of discontinuing patients from ART if necessary (and thus from study participation). In addition, a local data and safety monitoring committee consisting of site investigator, site coordinator, and a representative of the clinical monitoring service are responsible for assessing data quality and safety at each study site. National management consisting of LT, and NK, conducts additional supervision, provide training and guidance and assess compliance with the study protocol of all serious adverse events. As this is an investigator-initiated trial, there are no competing interests and the sponsor, the University of Oslo, Norway, is represented by the National PI (LT).

All relevant study personnel are trained in ICH-GCP and CTCAE event registration. All participants are insured against SAEs attributable to study drug (XR-NTX) occurring during or after participation via the Sponsor’s membership in the Norwegian Drug Liability Association.

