#### Outcomes & instruments

Urine Drug Test (UDT) data will be analyzed in accordance with recent Cochrane specifications as either a) proportion of total number of UDTs without illicit opioids or b) number of UDTs negative for illicit opioids received from each patient in each group during the 12-week randomized period [37].

Retention in treatment is defined in two ways: Number of days (of maximum 84 days) receiving effective pharmacological treatment, and number of patients completing the study at Week 12.

At baseline and every 4 weeks, patients undergo a structured interview and a selection of patient-reported outcomes: The European version of the Addiction Severity Index (the Europ-ASI) [38, 39] comprises drug and alcohol use, physical and mental health, work, education, social relations, and criminal behavior. The Europ-ASI is used for the second main drug use outcome measure, the number of days of abstinence from illicit opioid use in the 28 days preceding each interview for a total (maximum) of 84 days. To increase accuracy of responses relative to the Europ-ASI standard, timeline follow-back is used: a technique of backtracking and questioning about use and abstinence to obtain as accurate an estimate as possible of total number of days’ use of a specific substance in the 28-day follow-up period [40].

In addition to the primary outcomes, we explore secondary outcomes of importance to recovery: Number of patients fulfilling MINI [36] (DSM-IV) criteria for dependence on illicit opioids (exempting the 12-month criterion). The Addiction Severity Index administered every 4th week also records information on the use/abuse of alcohol, amphetamines, cannabis, sedatives (e.g. benzodiazepines), as well as other illicit substances (e.g. LSD, MDMA, GHB), and poly-drug use; days of injecting drug use; any overdoses (non-lethal) and hospitalizations in somatic or psychiatric health care; workdays and days engaged in illegal activities; number of days with conflicts in close relations, days physical and mental illness.

Craving for heroin is assessed using a 0–10 Visual analogue scale (VAS) on two questions: ‘I need heroin’ where ‘0’ signifies ‘Strongly disagree’ and 10 ‘Strongly agree’; and ‘How much have you been bothered by thinking about opioids or their use in the past 4 weeks?’ with 0 indicating ‘not at all’ and 100 ‘constantly’.

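### The stated imputation, last observation or inclusion value carried forward, freezes status after dropout and biases the self-reported abstinence comparison in an unpredictable direction

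*Protocol article*

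**What the plan says.** The Analysis sets section plans that "Intention-to-treat (ITT) analyses of efficacy endpoints will be conducted with all patient data", alongside an analysis of completers. For missing data it gives a definite rule: "Imputation will be conducted using the previous valid assessment (last observation carried forward) at the last attended study follow-up". The fallback is the value recorded at entry, "if no follow-up took place) from the inclusion dataset". Two options are left open. First, "imputation using data modeling may be considered pending satisfactory similarity to collected data". Second, "The inclusion dataset may be corrected for days spent in a controlled environment". The second matters because "Detoxification and induction on to study medication is conducted in a controlled environment, usually an on-site inpatient detoxification unit".

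The outcomes it could touch are defined under Outcomes & instruments. Self-reported abstinent days are collected by interview every 4 weeks, in three 28-day windows to a maximum of 84. Urine tests are weekly and are summarised either as a proportion of all tests or as the "number of UDTs negative for illicit opioids received from each patient in each group during the 12-week randomized period". Statistical analyses names a mixed model for between-group comparisons, and Kaplan-Meier with a log-rank test for retention. Determination of sample size assumes 70% retention at Week 12 in both arms.

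**The concern.** Carrying the last value forward assumes that a patient's drug use stays as it was when last seen. The protocol argues the opposite: the Background describes opioid addiction as chronically relapsing, and the Discontinuation section notes that overdose risk rises when treatment stops. A patient abstinent at the Week 4 visit who then leaves and relapses is credited with abstinence for the next 56 days.

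Three further problems follow.
- A single filled-in value is analysed as if it had been observed, so the reported uncertainty is generally too small.
- A patient with no follow-up receives an inclusion value that may or may not be corrected for days in a controlled environment, so the same patient can be given two different scores.
- The open door to modelled imputation depends on resemblance to the collected data, which is no test of whether dropouts resemble those who stayed.

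At stake is a primary outcome, self-reported abstinence, in a trial that wants to be able to conclude either superiority or equal effectiveness.

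**Working it through.** The protocol gives no figure for the effect of its imputation rule, so there is none to reproduce. What follows is an illustration.

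**Inputs from the protocol.** Three 28-day windows, 84 days in all. Retention 70%, so 30% dropout; of the planned 90 per arm that is 0.30 × 90 = 27 patients. I assume that leaving treatment also means missing the later interviews.

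**Assumed inputs.**
- On-treatment share of days abstinent p_on = 0.58 (borrowed from the planning rate of 7/12 negative urines), and 0.33 (4/12) where a second rate is needed.
- Share after dropout p_off = 0.10.
- Dropout in equal thirds (10% each) at the start of the Week 4, Week 8 and Week 12 windows.
- Inclusion value b = 0.10 if corrected. If uncorrected with 14 of 28 days in detoxification, b = (14 + 14 × 0.10)/28 = 0.55.

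**Step 1: inflation of one arm mean.** Patients lost before Week 4 carry b for three windows. Those lost before Week 8 carry p_on for two windows, and those lost before Week 12 for one.

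Inflation = 0.10 × 84 × (b − p_off) + 0.10 × 28 × (2 + 1) × (p_on − p_off) = 8.4 × [(b − p_off) + (p_on − p_off)]

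- Corrected: 8.4 × (0 + 0.48) = 4.0 days.
- Uncorrected: 8.4 × (0.45 + 0.48) = 7.8 days.

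The true arm mean is 0.70 × 48.72 + 0.10 × 8.40 + 0.10 × 21.84 + 0.10 × 35.28 = 40.7 days. Carry-forward gives 44.7 or 48.5.

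**Step 2: sensitivity to the assumptions.** Inflation in days:

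| p_off | b = 0.10 | b = 0.55 |
|---|---|---|
| 0.10 | 4.0 | 7.8 |
| 0.20 | 2.4 | 6.1 |
| 0.30 | 0.7 | 4.5 |

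The gap between the columns is always 8.4 × 0.45 = 3.8 days and is due to the optional correction alone. With 7 rather than 14 days in detoxification, b = (7 + 21 × 0.10)/28 = 0.325, and the first row gives 8.4 × (0.225 + 0.48) = 5.9.

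**Step 3: direction of bias in the difference.** For the last window, truth = (1 − d) × p_on + d × p_off and carry-forward = (1 − d) × p_on + d × last value, where d is the dropout share. p_off = 0.10. The last value is p_on except in the final row. Arms are XR-NTX / BP-NLX.

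| p_on | Dropout | True difference | Carried forward |
|---|---|---|---|
| 0.58 / 0.58 | 40% / 20% | 0.388 − 0.484 = −0.096 | 0.000 |
| 0.58 / 0.33 | 40% / 20% | 0.388 − 0.284 = +0.104 | +0.250 |
| 0.58 / 0.33 | 30% / 30% | 0.436 − 0.261 = +0.175 | +0.250 |
| 0.58 / 0.33 | 20% / 40% | 0.484 − 0.238 = +0.246 | +0.250 |
| 0.58 / 0.33, last value 0.10 | 40% / 20% | +0.104 | +0.104 |

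The rule hides a difference in the first row, exaggerates it in the second and third, and leaves it nearly or wholly unchanged in the last two.

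**Step 4: what the alternatives give in the Step 1 example.** A model fitted to observed visits under missing at random sees only 0.58 and estimates 0.58 × 84 = 48.7 days. Scoring missing windows as use gives 0.70 × 48.72 + 0.10 × 16.24 + 0.10 × 32.48 = 39.0 days. Together they bracket the true 40.7.

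**The case against.** The strongest objection is that carry-forward transmits use as faithfully as abstinence. A patient using at the last visit stays scored as using, and a properly corrected inclusion value will mostly reflect use. That stands, and the last row of Step 3 shows it.

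A reader might therefore go too far in inferring that the rule scores dropouts as abstinent in general, pulls the arms together and so favours a finding of equal effectiveness. The documents do not support this. Convergence appears when on-treatment rates are assumed equal; at the protocol's own planning rates the rule mostly widens the difference or leaves it alone. The only stated margin is 20 points on retention, which is analysed without imputation.

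A reader might also express the damage in weekly urine tests. The rule refers to attended follow-ups, which the Outpatient follow-up section distinguishes from weekly tests. If negative tests received are counted without imputation, a dropout simply adds none. The text does not exempt urine tests, however, so the point is worth settling.

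A third tempting inference is that stopping study medication generally ends data collection. The sentence in question, "with the option of discontinuing patients from ART if necessary (and thus from study participation", concerns patients whom the ART services discontinue from ART, not everyone who stops a study drug.

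Finally, the mixed model is no cure in itself. Step 4 shows that it can overestimate as much as carry-forward when dropouts relapse unobserved. That objection stands and shapes the fix. It does not rescue a rule that relies on an implausible assumption, understates uncertainty and depends on an optional correction.

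**Conclusion.** The concern holds in this form: the protocol fixes a poor imputation rule for its intention-to-treat efficacy analyses, and the rule should be replaced. It is a stated choice, not a detail left to an analysis plan. The affected primary outcome is self-reported abstinent days. Retention is untouched, and the urine count is untouched if not imputed.

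In the illustration an arm mean is inflated by about 4.0 days (corrected inclusion value) or 7.8 days (uncorrected), on a true mean of 40.7 out of 84. These figures rest on the assumed abstinence rates, dropout timing and 14 detoxification days, and on equating loss from treatment with loss from follow-up. They fall to 0.7 and 4.5 days if 0.30 of days are abstinent after dropout. The direction of bias in the comparison cannot be predicted from the documents.

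**What to change.** Delete carry-forward of the last observation and of the inclusion value as the imputation rule. Then:

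- **Self-report:** analyse the 4-weekly abstinent days with the planned mixed model on all observed visits, with visit and treatment-by-visit terms, or with multiple imputation. State that either assumes missing at random.
- **Sensitivity analysis for self-report:** score missing periods as use, so that the result does not rest on missing at random alone.
- **Urine tests:** do not carry results forward. Count negative tests received out of the 12 scheduled. This already treats a missing test as not negative, so a separate analysis with missing as use would only duplicate it.

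The cost is slightly more analysis work and possibly less favourable abstinence estimates. No clinical procedure changes.
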